### Clinical effectiveness

#### Primary clinical outcome

In positive psychology, positive mental health refers to the presence of human strengths, including a state of emotional, psychological, and social well-being, which empowers individuals to embrace life and build resilience in challenging conditions [41]. Positive mental health will be measured among patients and their loved ones in both studies using the Mental Health Continuum Short Form (MHC-SF). The MHC-SF is used to assess positive mental health in general population studies using 14 items across 3 subscales. The subscales are emotional wellbeing (3 items), social wellbeing (5 items) and psychological wellbeing (6 items). The items reflect the frequency of several feelings in the past month, which are rated ordinally using a 6-point Likert scale: never, once or twice a month, about once a week, two or three times a week, almost every day, and every day. The Dutch version of the MHC-SF has shown a high degree of validity and reliability in the general adult Dutch population. The reliability of the MHC-SF was characterized by a Cronbach’s alpha of 0.89 for the total scale, 0.74 for the subscale of social wellbeing and 0.83 for the subscales of both emotional wellbeing and psychological wellbeing [46]. Due to the small sample size of study 1, the MHC-SF in this study will only be used for measuring preliminary effects within individuals without aiming to guide study adjustments or to establish clinical effectiveness. In study 2, however, the MHC-SF is defined as the primary outcome for clinical effectiveness.

#### Secondary clinical outcomes

In both studies, patients and their loved ones will complete questionnaires designed to measure secondary outcomes within positive psychology, including self-compassion (Self-Compassion Scale – Short Form; SCS-SF) [67], savouring (Savouring Beliefs Inventory; SBI) [68], optimism (Life Orientation Test – Revised; LOT-R) [69], gratitude (Dutch gratitude questionnaire; GQ6) [70], and resilience (Brief Resilience Scale; BRS-NL) [71]. Additional secondary outcomes will be measured among patients and their loved ones, including physical and psychological symptoms (Brief Symptom Inventory; BSI) [72], depression (Patient Health Questionnaire; PHQ-9) [73], and relational satisfaction (Relational Satisfaction Scale; RSS) [74]. All questionnaires are measured ordinally using different Likert scales. Since their applicability extends beyond mental healthcare, these questionnaires have been used in the general Dutch (working) population and adolescent/adult mental health populations. Due to the small sample size of study 1, the SCS-SF, SBI, LOT-R, GQ-6, BRS-NL, BSI, PHQ-9, and RSS in this study will only be used for measuring preliminary effects within individuals without aiming to guide study adjustments or to establish clinical effectiveness. In study 2, however, these questionnaires are all defined as secondary clinical outcomes in study 2.

SCS-SF: the SCS-SF is a 12-item questionnaire measuring six subscales of self-compassion: self-kindness, self-judgment, common humanity, isolation, mindfulness, and over-identification. Each subscale contains two items. To measure each item, the SCS-SF employs an ordinal 5-point Likert scale, ranging from ‘’almost never’’ to ‘’almost always’’. Since Cronbach’s alpha was 0.86, the scale was considered consistent and reliable [67].

SBI: The SBI is a 24-item questionnaire measuring beliefs about savouring (i.e., the ability to appreciate and enhance everyday life), using three 8-item subscales: anticipating pleasure, present moment pleasure, and reminiscing pleasure. Each item is measured ordinally using a 7-point Likert scale, ranging from ‘’strongly disagree’’ to ‘’strongly agree’’. Although a Dutch adaptation is currently not validated, a French version of the SBI was considered internally consistent. Within this SBI version, the three subscales of anticipating pleasure, present moment pleasure, and reminiscing pleasure were characterized by a favourable McDonald’s Omega coefficients of 0.88, 0.86, and 0.85, respectively [75].

LOT-R: the LOT-R is a 10-item questionnaire measuring dispositional optimistic tendencies (i.e., the general tendency to expect positive future outcomes) in two 3-item subscales: optimism and pessimism. The remaining four 4 items are considered fillers. Using a same-day recall period, the LOT-R employs an ordinal 5-point Likert scale to measure all items, ranging from ‘’strongly disagree’’ to ‘’strongly agree’’. A Dutch version of the LOT-R was considered sufficiently internally consistent, based on intraclass correlation coefficients (test-retest reliability) of 0.74 and 0.67 for the subscales of optimism and pessimism, respectively [76].

GQ-6: Apart from measuring optimistic tendencies, the GQ-6 will be used to measure 6 items on gratitude in everyday life using a current-day recall period. Subscales are absent. All items in the GQ-6 are measured ordinally using a 7-point Likert scale, ranging from ‘’strongly disagree’’ to ‘’strongly agree’’. Based on a McDonald’s Omega of 0.75, a Dutch adaptation of the GQ-6 has demonstrated acceptable internal consistency [70].

BRS-NL: the BRS-NL is a Dutch 6-item questionnaire reflecting general resilience traits, using a present-day recall period. The BRS-NL does not contain subscales. Items are measured ordinally using a 5-point Likert scale, ranging from ‘’strongly disagree’’ to ‘’strongly agree’’. Since a Cronbach’s alpha of 0.74 was determined, the BRS-NL has shown acceptable internal consistency [71].

BSI: The BSI is a 53-item questionnaire measuring self-reported psychological and physical symptoms in adult and adolescent mental health populations in Dutch clinical practice, such as grief, anxiety, depression and headaches. Using a 7-day recall period, the BSI measures 9 subscales: somatization, cognitive complaints, interpersonal sensitivity, depression, anxiety, hostility, phobias, paranoid thoughts, and psychoticism. All items are rated ordinally on a 5-point Likert scale, ranging from ‘’not at all’’ to ‘’extremely’’. With Cronbach’s alpha ranging between 0.76 and 0.97 for the 9 subscales, a Dutch version of the BSI was considered internally consistent [72].

PHQ-9: Next, the PHQ-9 is a 9-item questionnaire without subscales. It is primarily used to screen for depressive symptoms in adult and elderly populations suffering from depressive symptoms due to chronic physical illnesses. Using a two-week recall period, the items are measured ordinally on a 4-point Likert scale, ranging from ‘’no’’ to ‘’almost every day’’. With an internal consistency of 0.88 and test-retest reliability of 0.94, a Dutch version of the PHQ-9 was considered highly reliable in a general Dutch primary care sample [77].

RSS: Finally, the RSS is a 12-item questionnaire on certain domains regarding the perceived quality of human relationships, without subscales. This may include intimate relationships, as well as work related relationships, family ties and friendships. This questionnaire was initially applied in the general adult UK population. Using a same-day recall period, all items are measured ordinally on a 6-point Likert scale, ranging from ‘’very dissatisfied’’ to ‘’very satisfied’’. The original version of the RSS was internally consistent with a Cronbach’s alpha of 0.89, indicating strong reliability [74].

#### Collecting background variables for longitudinal change trajectories

In study 2 (RCT), change trajectories within subpopulations of the research sample and between the RCT arms will be modelled over a prolonged period of time. To prepare this modelling process, data on background variables needs to be collected. Based on theoretical considerations, background data on certain demographics (i.e., education and literacy, employment status, sex, and age) and clinical profiles (i.e., severity of psychological complaints, and diagnosis) will be used. Data on these demographic characteristics will be obtained using a separate question about each characteristic. Lastly, data on clinical profiles will be gathered using the aforementioned BSI questionnaire and a separate question on self-reported diagnosis.

### Economic evaluation

#### The application of previously described clinical outcomes for the CEA

In the CEA of study 2, certain outcome variables for assessing clinical effectiveness will also be used to evaluate cost-effectiveness. In the CEA, the aforementioned measure for positive mental health (MHC-SF) will be defined again as the primary outcome. Secondary outcomes will include all scores obtained from the previously mentioned BSI and BRS-NL.

#### Measuring quality adjusted life years for the CUA

In the CUA of study 2, new outcome measures will be collected, including scores on the EuroQol 5-Dimension 5-Level questionnaire (EQ-5D-5L) [78, 79]. The EQ-5D-5L will be used to derive Quality Adjusted Life Years (QALYs), which is defined as the primary outcome in the CUA. The EQ-5D-5L questionnaire is primarily used to assess quality of life in either the general population or subpopulations facing debilitating illness. Given the absence of subscales, the EQ-5D-5L includes 5 items encompassing 5 dimensions related to quality of life: mobility, self-care, daily activities, pain/discomfort, and anxiety/depression. These items are measured ordinally using a same-day recall period, with multiple-choice responses ranging from ‘’no problems’’ to ‘’extreme difficulties’’. With Gwet’s Agreement Coefficient ranging from 0.64 to 0.97 for the 5 dimensions, a Dutch version of the EQ-5D-5 L was considered reliable [80]. However, the clinical meaning of EQ-5D-5 L scores in patients facing mental health complaints has been criticized [81].

To address these concerns in the CUA, adjusted utility scores for estimating quality of life will be measured using the ICEpop CAPability measure for Adults (ICECAP-A) [82] with accompanying Dutch ICECAP-A tariffs [83]. The ICECAP-A was primarily developed to measure human capabilities for generating mental and physical wellbeing in the general adult UK population, using a same-day recall period. Five dimensions (items) of human capabilities are rated: stability, attainment, autonomy, achievement, and enjoyment. All capability items are rated, using an ordinal 4-point scale ranging from low to high. A Dutch version of the ICECAP exists as well, which is characterized by an intraclass correlation of.79. and thus adequate test-retest reliability [84]. In addition, the mental health quality-of-life questionnaire (MHQoL) will be used [85] with accompanying Dutch MHQoL tariffs [86]. Contrary to the generic EQ-5D-5L, the MHQoL aims to specifically measure quality of life in people with mental health issues. Using a same-day recall period, the MHQoL employs a visual analog scale for numerically rating psychological wellbeing and the following 7 dimensions (items) for rating psychological quality of life: self-image, independence, mood, relationships, daily activities, physical health, and the future. In particular, these 7 items are measured ordinally, using 4 response levels ranging from ‘’very satisfied’’ to ‘’very dissatisfied’’. With a Cronbach’s alpha of 0.85, a Dutch version of the MHQoL was considered internally consistent and reliable [85].

#### Measuring societal costs for the CEA and CUA

In both the CEA and CUA, costs will be measured among patients from a societal perspective, including healthcare costs (i.e., health services use and medications), productivity losses (i.e., absenteeism and presenteeism), and intervention costs (i.e., the costs of implementing the intervention). To measure healthcare costs and productivity losses, a 3-month recall period will be used. Consumption of health services, medications, and productivity losses in patients facing psychological complaints will be measured, using the Treatment Inventory of Costs in Patients with psychiatric disorders (TIC-P) [87].

By definition, the TIC-P was developed as a generic questionnaire to estimate societal costs across all Dutch adult mental health populations within inpatient and outpatient clinical settings. Using both categorical multiple choice and numerical open ended questions, the TIC-P aims to measure 3 subscales: general demographics (7 items), healthcare consumption (38 items), and productivity losses in both the formal and informal workspace (12 items) [87]. In the absence of subscale estimates (e.g., Cronbach’s alpha) on reliability, Cohen’s Kappa was still considered highly satisfactory for most separate items on healthcare consumption, and satisfactory for most items on productivity losses [88]. Productivity losses in the workspace are based on absenteeism (i.e., not being able to work) and presenteeism (i.e., reduced productivity in the workspace). Informal productivity losses related to unpaid work will also be measured. Patients will report their hours of absence (i.e., absenteeism) and the additional hours they needed to finish work due to health complaints (i.e., presenteeism).

In addition, intervention costs related to the implementation of the eHealth PPI will be prospectively recorded during the trial using a Microsoft Excel sheet. Following the recent guidelines for economic evaluation issued by Zorginstituut Nederland (ZIN) [65], the measured intervention cost categories are: [1] personnel time, [2] training costs, [3] licensing and platform maintenance, [4] development costs, and [5] technical support. If possible, annual invoices from the participating eHealth organization will be used to assess relevant eHealth PPI implementation costs. More specifically, [1] personnel time includes the amount of time spent by healthcare staff to supervise participants during the eHealth PPI (e.g., providing feedback and responding to alerts). This time investment is a variable cost component and will be derived using digital logs on the eHealth platform and self-reported tracking by staff members from the eHealth organization and Open University. If applicable, [2] additional training costs related to good supervision practices among staff members will be documented as fixed costs, including required resources and preparation time. Annual fees related to [3] licensing and platform maintenance will be retrieved from invoices provided by the eHealth organization. If not covered by licensing fees, additional [4] development costs related to the eHealth software will be recorded and treated as fixed costs, based on provider documentation from the eHealth organization. If [5] technical support costs for participants (e.g., IT helpdesk support) are invoiced separately from licensing and service agreements, the frequency and variable costs per user will be measured using these invoices. Lastly, all healthcare, non-healthcare and intervention cost components will eventually be valued, using the most recent costing manual in Dutch healthcare [66].

### Implementation procedures

#### Measuring procedural constructs

The holistic framework for eHealth evaluation proposed by van Gemert-Pijnen, Nijland [89] will be used to inform an evaluation of eHealth PPI implementation procedures, emphasizing context-sensitive evaluation by employing a participatory approach, advanced mixed methods, and timely measurements of process constructs prior to and during the studies. Guided by these framework principles, five procedural constructs will be addressed from a user-perspective: feasibility, accessibility, adherence, engagement, and acceptability. To measure these constructs, the following measurement methods will be used: written stakeholder feedback, the System Usability Scale (SUS), login frequency data, and post-module process questions. Each measurement method will be explained below.

##### Written stakeholder feedback

Prior to implementing both studies, various stakeholders within the participating mental health clinic will be consulted by e-mail. More specifically, at least five patient representatives, one care manager and one mental health professional will provide written feedback on a digital concept version of the eHealth PPI, which will be used to improve the intervention modules prior to performing study 1 and study 2 [90].

##### System Usability Scale (SUS)

While feasibility refers to the perceived usability and functionality of the eHealth PPI, accessibility examines participants’ ease of access to the eHealth PPI, considering technological literacy [91]. The System Usability Scale (SUS) [92], which is a 10-item questionnaire assessing the perceived usability of digital tools using an ordinal 5-point Likert scale ranging from ‘’strongly disagree’’ to ‘’strongly agree’’, will be used to measure feasibility and accessibility in both studies. The SUS was initially developed to examine adult populations interacting with digital tools. With a Cronbach’s alpha of 0.74, a Dutch version of the SUS was considered internally consistent and reliable for usability assessment [93].

##### Login frequency data

To further explore the accessibility of the eHealth PPI, differences in PPI starting time among participants (i.e., the time between providing informed consent and starting the first PPI module) will be measured in both studies using login frequency data from the eHealth platform. Adherence, defined as the extent to which study participants comply with the basic eHealth PPI protocols (i.e., moving through all required tabs within a module and finishing digital homework assignments), will also be measured in both studies using login frequency data. Lastly, the same login frequency data aims to measure engagement in both studies, defined as the depth of interaction between study participants and the modules of the eHealth PPI. In this context, engagement is measured by assessing both the total time spent on each PPI module and the interactions between study participants and the optional drop-down menus within each PPI module, including additional information and homework assignments.

##### Post-module process questions

The overall acceptability of the eHealth PPI will be measured in both studies using [1] a quantitative rating question and [2] a qualitative, open question after each PPI module (i.e., post-module process questions), requesting study participants: [1] to rate their satisfaction regarding each PPI module on a scale from 1 to 10, [2] to explain their rating in their own words, focusing on the content, features and layout of each PPI module. In addition to measuring acceptability, these post-module process questions may also yield quantitative and qualitative data on the other process constructs (i.e., feasibility, accessibility, adherence, engagement) of the entire eHealth PPI.

### Visual overview of data collection in both studies

The aforementioned questionnaires will be used at several points in time during study 1 and study 2. In both studies, the time spent on each measurement will be at most 30 min. An overview of all proposed measurements for patients and loved ones in both studies is presented in Tables 1 and 2.

**Table 1 Tab1:** All questionnaires for each measurement in study 1 (RSCD) among patients and loved ones

	T0:pre-PPI-measurement	T1: measure following module 1	T2: measure following module 2	T3: measure following module 3	T4: measure following module 4	T5: measure following module 5	T6: measure following module 6	T7: measure following module 7	T8: measure following module 8	T9: measure following module 9
MHC-SF	*x **				x *					x *
BSI	*x **									x *
SUS										*x **
Post-module process questions		*x **	*x **	*x **	*x **	*x **	*x **	*x **	*x **	*x **
Clinical profile	*x*									
Demographics	*x **									
Expectations	*x **									
PHQ-9	*x**									*x**
RSS	*x **									*x **
LOT-R	*x **								*x **	*x **
SCS-SF	*x **		*x **	*x **						*x **
SBI	*x **					*x **	*x **			*x **
GQ-6	*x **							*x **		*x **
BRS-NL	*x **									*x **

*x* = patient; ***= loved one; *MHC-SF* Mental Health Continuum – Short Form, *BSI* Brief Symptom Inventory,* SUS* System Usability Scale; Post-module process questions = questions related to the performance of each PPI module from a process evaluation perspective; Clinical profile = mental health complaints, symptomatic severity; Demographics = sex, age, income, education; Expectations = participant expectations regarding the eHealth PPI *PHQ-9* Patient Health Questionnaire – 9, *RSS* Relational Satisfaction Scale, *LOT-R* Life Orientation Test – Revised, *SCS-SF* Self-Compassion Scale – Short Form, *SBI* Savoring Beliefs Inventory, GQ-6 = Gratitude Questionnaire – 6; BRS-NL = Brief Resilience Scale – NL

**Table 2 Tab2:** All questionnaires for each measurement in study 2 (RCT) among patients and loved ones

	T0: Pre-PPI measurement	T1: Post-measure following immediate PPI completion	T2: 3-month measure following PPI completion	T3: 6-month measure following PPI completion	T4: 9 month measure following PPI completion	T5: 12-month measure following PPI completion	T6: 12-month measure following treatment completion
MHC-SF	*x **	*x **	*x*	*x*	*x*	*x*	*x*
BSI	*x **	*x **	*x*	*x*	*x*	*x*	*x*
SUS		*x **					
Post-module process questions		*x **					
Clinical profile	*x*						
Demographics	*x **						
Expectations	*x **						
PHQ-9	*x**	*x**					
RSS	*x **	*x **					
TIC-P	*x*	*x*	*x*	*x*	*x*	*x*	*x*
EQ-5D-5 L	*x*	*x*	*x*	*x*	*x*	*x*	*x*
MHQoL	*x*	*x*	*x*	*x*	*x*	*x*	*x*
ICECAP-A	*x*	*x*	*x*	*x*	*x*	*x*	*x*
LOT-R	*x **	*x **					
SCS-SF	*x **	*x **					
SBI	*x **	*x **					
GQ-6	*x **	*x **					
BRS-NL	*x **	*x **	*x*	*x*	*x*	*x*	*x*

*x* = patient; ***= loved one; MHC-SF = Mental Health Continuum – Short Form; BSI = Brief Symptom Inventory; SUS = System Usability Scale; Post-module process questions = questions related to the performance of each PPI module from a process evaluation perspective; Clinical profile = mental health complaints, symptomatic severity; Demographics = sex, age, income, education; Expectations = participant expectations regarding the eHealth PPI; PHQ-9 = Patient Health Questionnaire – 9; RSS = Relational Satisfaction Scale; TIC-P = Treatment Inventory of Costs in Patients with psychiatric disorders; EQ-5D-5 L = EuroQol 5-Dimensions 5-Levels; MHQoL = Mental Health Quality of Life; ICECAP-A = ICEpop CAPability measure for Adults; LOT-R = Life Orientation Test – Revised; SCS-SF = Self-Compassion Scale – Short Form; SBI = Savoring Beliefs Inventory; GQ-6 = Gratitude Questionnaire – 6; BRS-NL = Brief Resilience Scale – Netherlands

## Data analysis

All analyses of (cost-)effectiveness will be performed in accordance with the Intention-To-Treat (ITT) principles, meaning that data from all participants will be analysed according to the study condition to which they were initially assigned, regardless of adherence [94]. Assessment of baseline inequalities between study conditions will be performed and followed up, if needed. Due to the longitudinal nature of study 1 and study 2, dropout and other processes causing missing data are expected [95]. Appropriate missing data handling techniques will be applied after assessment of the magnitude, mechanisms, and patterns of missing data [96]. A one-sided alfa of 0.05 will be applied in both studies. Since multiple comparisons between RCT arms will be performed in study 2, this significance level of 0.05 will be adjusted to manage Type I error probability, using the Holm-Bonferroni method [97].

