### Clinical effectiveness

#### Primary objective

Our primary clinical aim is to examine whether offering the eHealth PPI to various patients during the waiting period and their loved ones, followed by a mental health treatment for patients, is clinically effective in terms of improving positive mental health scores (primary outcome) at the 6-month and 12-month post-PPI measurement, compared to TAU. We hypothesize that introducing this eHealth PPI in condition 1 (PPI for patients only) and in condition 2 (PPI for patients and loved ones), followed by a mental health treatment, is clinically more effective, compared to condition 3 (TAU).

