**Fig. 1 Fig1:**
[figure not shown]
Flowchart of the proposed RCT (study 2). Note: *Predicted start of the official intake and a mental health treatment for most patients: Although the official intake and treatment could take place in principle after the pre-measurement, most patients will likely receive treatment more than 5 weeks after completion of the first post-measurement due to long waiting times in Dutch mental healthcare (i.e., > 14 weeks)

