#### Secondary analyses

The secondary clinical analyses of study 2 aim to evaluate whether the eHealth PPI significantly affects other outcome measures, in addition to examining the effects of including loved ones in the eHealth PPI. Outcome scores on the other positive psychology constructs (i.e., SCS-SF, SBI, LOT-R, GQ-6, and BRS-NL), physical and psychological symptoms (i.e., BSI), depression (i.e., PHQ-9), and relational satisfaction (i.e., RSS) will be addressed in both studies. In study 2, an ANCOVA will be used again, employing the pre-PPI-measurement as a covariate. Using this method, a comparison will be made between the pre-PPI measurement and the immediate post-PPI measurement to analyse the scores on the SCS-SF, SBI, LOT-R, GQ-6, BRS-NL, BSI, PHQ-9, and RSS across the three independent RCT conditions. Using this approach, the effects of including loved ones in the second condition *(eHealth PPI for patients and loved ones)* will also be examined, relative to the other conditions. An additional visual analysis — considered foundational for single-case designs [98] — will be employed in study 1 to identify preliminary effects within individuals for descriptive purposes without aiming to establish clinical effectiveness or to guide study adjustments.

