In study 2, multilevel regression modelling will be used to examine and compare the average longitudinal trajectory of change on the primary outcome (i.e., MHC-SF) across the three RCT arms. Based on theoretical considerations, certain demographics (i.e., education and literacy, employment status, sex, and age) and clinical profiles (i.e., severity of psychological complaints, and diagnosis) are considered relevant group-level moderators for modelling such change trajectories. Using these moderators in a multilevel regression model, moderation analyses will be employed to examine variations in longitudinal change trajectories between the RCT conditions on the primary outcome (i.e., MHC-SF) and relevant secondary outcomes (i.e., BSI, MHQoL, and BRS-NL) across the seven RCT measurement points. Using the same moderation analyses, the average trajectory of change for certain subpopulations will be examined across the seven RCT measurement points to evaluate how different subpopulations respond to the eHealth PPI over time. Notably, moderation analyses for subpopulations may reveal different associations between group-level moderators and PPI effectiveness, even if these associations cancel each other out in the overall change comparisons between the three RCT conditions [99].

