During the waiting period, a patient’s health status may deteriorate as a result of symptomatic aggravation, which may or may not become an adverse event [9]. Using a safety plan and a disclaimer in the eHealth PPI, patients will be informed on how to reach out to their local GP or urgent care GP. Participants are asked to fill out this safety plan during the first week of participation. In this safety plan and in each intervention module, the following disclaimer will be presented: *‘’Support during this study will primarily be offered through email contact. However*,* your emails may not be answered on a daily basis. Therefore*,* this form of communication is insufficient in urgent cases. In case of an emergency*,* you should always contact your general practitioner.’’* Potential side effects and clinical benefits will be explained to patients and their loved ones, using a comprehensive participant information letter. In severe cases, included patients may be hospitalized in an inpatient mental health clinic. While hospitalized patients are ethically allowed to continue using the eHealth PPI, many of them will likely drop out.

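### The single one-sided alpha of 0.05 does not fit the secondary and moderation analyses, which have no stated direction; read as benefit tests, the BSI and PHQ-9 contrasts have no rejection region for worsening

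*Protocol article*

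**What the plan says.** The opening paragraph of Data analysis (Protocol article) sets the rule: "A one-sided alfa of 0.05 will be applied in both studies". It then says that, because several arms are compared, "this significance level of 0.05 will be adjusted to manage Type I error probability, using the Holm-Bonferroni method". Neither sentence gives a direction or exempts an outcome or type of analysis.

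The other relevant places are:

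- **Primary objective, Clinical effectiveness.** The hypothesis is that the PPI in conditions 1 and 2, followed by treatment, "is clinically more effective, compared to condition 3 (TAU"). This is directional and concerns positive mental health.
- **Secondary clinical outcomes.** Of the SCS-SF, SBI, LOT-R, GQ-6, BRS-NL, BSI, PHQ-9 and RSS, the section says that "these questionnaires are all defined as secondary clinical outcomes in study 2".
- **Secondary analyses.** The stated aim is to see whether the PPI has a significant effect on the other outcomes, with no direction given. The method is a three-arm ANCOVA in which "a comparison will be made between the pre-PPI measurement and the immediate post-PPI measurement to analyse the scores".
- **Secondary analyses, multilevel models.** Education and literacy, employment, sex, age, severity and diagnosis are moderators. The text notes that "moderation analyses for subpopulations may reveal different associations between group-level moderators and PPI effectiveness", even where these cancel out in the overall comparison.
- **Managing adverse events.** During the wait a patient's "health status may deteriorate as a result of symptomatic aggravation, which may or may not become an adverse event".
- **Table 2.** In patients, BSI is measured at T0 to T6 and PHQ-9 at T0 and T1.

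**The concern.** A one-sided test needs a side fixed in advance. The protocol supplies one for PPI versus TAU on the primary outcome. It supplies none for the moderators, and it foresees associations of opposite sign there. The secondary aim is also neutral. Applied as written, the rule therefore leaves these tests either undefined or given a side later.

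For the symptom scales the practical question is worsening. The protocol accepts that patients may deteriorate while waiting, and its Background says effectiveness is unknown in some of the diagnoses to be enrolled. TAU patients wait too, so the randomised contrast is what separates an effect of the PPI from an effect of waiting. T1 is the cleanest time for that contrast: the Fig. 1 note expects that "most patients will likely receive treatment more than 5 weeks after completion of the first post-measurement", and BSI and PHQ-9 are both taken then. If a PPI arm scored worse at T1, a benefit-directed contrast could report only a failure to show benefit.

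**Working it through.** The protocol gives no effect size, SD or power for BSI or PHQ-9, so it has no figure of its own to reproduce on this point.

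**Inputs**

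- From the A priori sample size section: 207 evaluable patients, 207/3 = 69 per arm; 207/(1 − 0.355) = 321 enrolled, 321/3 = 107 per arm.
- Assumed: 20% loss by T1, 0.80 × 107 ≈ 86 per arm.
- Assumed: true worsening d of 0.20, 0.30 or 0.45 SD. The largest value borrows the g used for MHC-SF.

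**Step 1. Benefit-directed one-sided contrast.** Its rejection region lies entirely on the benefit side. The chance of formally showing harm is 0 at any n and any d. Holm moves the critical value and adds no second tail.

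**Step 2. Two-sided 95% interval for PPI minus TAU.** With SD 1 and the normal approximation, nc = d × √(n/2). The interval lies wholly on the harm side with probability Φ(nc − 1.96), and its half-width is 1.96 × √(2/n). Example: n = 107 and d = 0.30 give nc = 0.30 × √53.5 = 2.194 and Φ(0.234) = 0.593.

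| n per arm | d = 0.20 | d = 0.30 | d = 0.45 | half-width (SD) |
|---|---|---|---|---|
| 107 (no loss by T1) | 0.310 | 0.593 | 0.908 | 0.268 |
| 86 (20% loss, assumed) | 0.258 | 0.503 | 0.839 | 0.299 |
| 69 (35.5% loss) | 0.216 | 0.422 | 0.753 | 0.334 |

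With an assumed baseline correlation of 0.5, nc is divided by √(1 − 0.25) = √0.75. At 107 per arm the probabilities become 0.393, 0.717 and 0.967.

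**Step 3. Three-arm ANCOVA F-test at 0.05.** The degrees of freedom are 2 and 3n − 4, and the noncentrality is n × the sum of squared deviations of the arm means. For means (d, d, 0) the deviations are d/3, d/3 and −2d/3, so the sum is (1/9 + 1/9 + 4/9)d² = (2/3)d². The means (0, d, 0) and (−d, −d, 0) give the same sum. At n = 107, F is significant with probability 0.305, 0.611 and 0.933 for the three values of d. These match the interval figures closely, but are identical whether both PPI arms are worse, only one is worse, or both are better by the same amount.

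**Step 4. Moderators.** If the side follows the observed sign, the rejection probability under no effect is 2 × 0.05 = 0.10.

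**Step 5. False harm signals with unadjusted intervals and no true effect.** Each interval falls on the harm side with probability 0.025.

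- Four T1 intervals (2 scales × 2 contrasts): at most 4 × 0.025 = 0.10; under independence, 1 − 0.975⁴ = 0.096.
- Fourteen intervals, if BSI is also read at T2 to T6 (7 × 2): under independence, 1 − 0.975¹⁴ = 0.298. Positive correlation lowers this.

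**The case against.** The strongest reply is that the direction for BSI and PHQ-9 is not stated. It is inferred from a primary objective about positive mental health, while the section governing these scales is neutrally worded. This stands, so the point about worsening is conditional. The neutral wording does not rescue the rule, however: a one-sided alpha with no side does not fit a neutral aim.

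It can also be said that the general sentence was meant only for the PPI-versus-TAU benefit hypotheses, since Holm adjustment of arm comparisons follows directly. That may be the intention, but the text sets no such limit.

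Third, the analysis named for BSI and PHQ-9 is a three-arm ANCOVA, whose F-test detects differences in either direction about as often as the proposed interval. This also stands. What F lacks is the arm and the direction.

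Fourth, an estimate with its standard error would still show worsening, nothing forbids reporting intervals, and adverse events are reported separately, with likely intervention-related SAEs distinguished. So a reader might infer that the trial cannot detect harm; the documents do not support that. What is lost is the formal directional pairwise conclusion. Individual event reports do not supply a randomised comparison of symptom scores.

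Fifth, detail on secondary outcomes may sit in an analysis plan that is not shown. Missing detail is not the complaint here. The protocol states a rule for both studies, and that rule does not suit part of what it covers.

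Lastly, the Fig. 1 note also says intake and treatment could in principle begin after the pre-measurement, so T1 is the cleanest reading without being perfectly clean.

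**Conclusion.** The concern holds in a limited form. The blanket one-sided rule does not fit the neutrally worded secondary aim or the moderation analyses. On the benefit-directed reading, the pairwise BSI and PHQ-9 contrasts have no formal rejection region for worsening. That zero follows from the form of the test. The contrasting figures, 31%, 59% and 91% at 107 per arm and 22%, 42% and 75% at 69, rest on assumed effects of 0.20, 0.30 and 0.45 SD and on the normal approximation.

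A reader might also infer that moderator tests will run at 10%. This happens only if the side is chosen after seeing the data, and the protocol does not say it will be. Nor does anything here affect the MHC-SF conclusion or the sample size. The change should be made, but it is a repair to secondary inference. Confidence is medium because the direction is inferred.

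**What to change.** In Data analysis, limit the one-sided 0.05 level with Holm adjustment to the hypotheses that each PPI arm is better than TAU. In Secondary analyses:

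- Report the PPI-minus-TAU differences in patients on BSI and PHQ-9 with two-sided 95% confidence intervals, unadjusted for multiplicity when read for worsening, with T1 as the main reading.
- Test the moderation effects two-sided.

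This is a change of wording and uses data already planned. The MHC-SF analysis, the benefit tests on BSI and PHQ-9 and the sample size stay as they are.

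The first cost is false alarms: at most about 10% across the four T1 intervals, and about 30% or less across 14 if later BSI time points are read the same way. The second is some power for moderators whose direction would have been guessed correctly. As an illustration, a one-sided 5% test with 80% power has nc = 1.645 + 0.842 = 2.487; tested two-sided at 5%, its power is Φ(2.487 − 1.96) = 0.70.
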